**Figure 1 fig1:**
[figure not shown]
Consolidated Standards of Reporting Trials (CONSORT) flow diagram.

### Setting and recruitment

Subjects will be recruited from relevant departments of three general hospitals in Anhui Province and offered gifts and free medical exams. Recruiters will present the study to breast cancer families who meet the study criteria. If patients and their families are interested in participating in this study, they will be asked to sign informed consent forms and randomly assigned. Investigators should explain to participating families that the study will not adversely affect them and that participating families can opt out of the study at any time.

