Due to the influence of traditional Chinese culture and the introverted nature of Chinese people, people are not used to expressing their feelings and sharing family problems publicly. This is consistent with what we learned earlier. Patients and their families prefer one-on-one family meetings. Therefore, one-on-one family meetings may be more effective than multifamily group meetings. Meanwhile, the postoperative treatment and follow-up of patients are mostly performed in local hospitals or outpatient clinics, and there is no time to participate in an intervention. In addition, repeatedly making appointments for patients and their families to come to the hospital to participate in an intervention increases the burden on the family and the risk of contracting COVID-19. Therefore, online meetings can solve these problems very well. The online meeting time and location are more flexible. Participants only need to find a relatively quiet place to join the meeting. The meeting time can also be adjusted if participants require it. Additionally, online meetings can be recorded. If some participants are absent due to personal reasons, they can learn about the content of the meeting from the video. Online meetings greatly improved the implementability and convenience of intervention programs.

Among the current family resilience intervention research, some studies are based on family resilience theory (Lim and Han, 2013; Inci and Temel, 2016; Miran, 2016), and some studies are based on other related theories (Chartier et al., 2010; Dorell et al., 2017; Wang, 2017; Faarup et al., 2019; Yu et al., 2020). Different theoretical foundations have different intervention programs, and the intervention effects also have certain differences. To this end, our research group [name] used grounded theory to study the formation process of family resilience of breast cancer patients, modeled the family resilience process of resilience among the families of breast cancer patients, and laid a theoretical foundation for formulating a breast cancer family resilience intervention program (Wu, 2020).

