### Sample size

Study sample size calculated by PASS15. Based on previous survey results (Lim and Han, 2013), family resilience measured by the Family Resilience Index (FHI) changed by 0.29 points before and after the intervention with a statistical power of 0.9, 2.5% significance, and using a one-tailed test to calculate a sample size of 36 families in each group (72 families in total; McCubbin et al., 1996). Assuming a 10% dropout rate in the intervention, each group would need to include 40 families (80 families in total). The sample size calculation formula is as follows:

$$n=\frac{{\left({Ζ}_{\alpha }+{Ζ}_{\beta }\right)}^{2*}2\sigma^{2}}{\delta^{2}}$$

A series of measures will be taken to reduce attrition during the intervention. First, during the intervention recruitment phase, the patient’s attending physician or other medical staff will be invited to answer the patient’s and family’s concerns to increase participants’ trust in the program. Second, a WeChat group will be established where researchers answer questions and share disease-related knowledge with participants. The third is to invite breast cancer treatment experts and nursing experts to control the quality of the entire intervention process, and timely answer questions from patients and their families about disease treatment and care. Fourth, during the intervention, participants can get in touch with the research team to get answers to any difficulties involved in the implementation and application of the intervention content. Finally, at the end of the program, the research team will present the participants with a nice gift to express their gratitude.

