Content	A brief recap of last week’s meeting. Let the primary caregiver to review issues encountered during the patient’s care over the past week. Combined with pictures and texts, it provides nursing methods and precautions for different treatments for breast cancer patients and their families. Have patients and primary caregivers share their emotions and stress over the past week. Help patients and primary caregivers learn ways to manage stress and emotions to stay positive and optimistic by combining pictures, text and videos.
Homework	Review the content of this meeting through electronic meeting materials. Patients and primary caregivers are encouraged to discuss their own stressors and ways to relieve stress with researchers (*via* voice or text message or phone call).
Family Organization - Family treasure (Third week after surgery)	
Theme	Discover Available Resources
Form	Online family meeting
Target	Identify the family’s own strengths and available resources and learn how to use them. Summarize the experience of overcoming difficulties from past experiences.
Content	A brief recap of last week’s meeting. Combine pictures and words to show participants’ families what family resources, social resources and family strengths are. Help family members discover and demonstrate their family strengths and resources. Discuss success and failure cases and their characteristics in overcoming difficulties through family conversations, and summarize experiences. Discuss together how to leverage existing family strengths and resources to address current issues and challenges. Encourage different families to exchange experiences through WeChat groups and provide emotional support to each other.
Homework	Review the content of this meeting through electronic meeting materials. Give researchers examples of how their resources will be used in the future (*via* voice or text message or phone call).
Family Organization - Intimacy has a way (Fourth week after surgery)	
Theme	Improve Family Cohesion
Form	Online family meeting
Target	Create simple and effective family rules to promote family relationships and strengthen family bonds.

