### Statistical analysis

Two investigators will enter and review data. SPSS23.0 will be used for data analysis with a one-tailed test and a significance level of 0.025. Descriptive analyses will be used for participants’ general data and the outcome variables, including means, standard deviations, and percentages. The t test or rank-sum test will be used for comparison if the baseline data of the two groups are continuous variables, and the chi-square test will be used for comparison if they are categorical variables. The effect of the intervention program will be assessed by observing changes in family resilience, coping styles, family disease burden, social support, anxiety and depression levels in the intervention and control groups. If the intervention effect within the group conformed to a normal distribution, the paired t test was used for evaluation; otherwise, the Wilcoxon rank-sum test was used. Repeated measures ANOVA will be used to assess the effect of the intervention at different time points between groups. AHP, multivariate adjustment analysis, and propensity score analysis will be used to control for confounding factors confounding the study results.

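### Families are assured without qualification that the study will do them no harm, although its effects are unknown and the one-tailed rule, read in the direction of the hypotheses, cannot conclude worsening

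*Protocol article*

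**What the plan says.** **What families are told.** The protocol article, Setting and recruitment, states: "Investigators should explain to participating families that the study will not adversely affect them". The same sentence gives families the right to leave at any time.

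**What is known about the programme.** The Introduction reports no earlier family resilience intervention study in breast cancer patients and says that this programme is to be validated here. The Discussion describes the field as immature, with effects that differ between programmes and remain uncertain.

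**What the sessions contain.** Table 1 has patients and caregivers share worries about the illness, sources of stress and current family problems, starting in the first week after surgery. The third-week entry reads: "Discuss success and failure cases and their characteristics in overcoming difficulties through family conversations, and summarize experiences".

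**How outcomes are tested.** Statistical analysis states: "SPSS23.0 will be used for data analysis with a one-tailed test and a significance level of 0.025". Sample size uses the same rule: "2.5% significance, and using a one-tailed test to calculate a sample size of 36 families in each group". All three statements under Hypotheses are of improvement. For the between-group comparison over time, Statistical analysis names repeated measures ANOVA.

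**What is measured.** Table 2 lists family resilience, coping, social support, family burden (FBSD), anxiety (SAS) and depression (SDS) at baseline and at three later visits. The instrument sections give severity bands for SAS and SDS and a threshold of 1 for each FBSD dimension.

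**The concern.** A trial is run because the effect of a programme is not known. To tell families that it cannot affect them adversely claims a result in advance, and nothing in the article supports the claim. The sessions ask people who have just had surgery, or who care for them, to talk about stress, setbacks and family problems. Temporary or lasting distress is a plausible outcome, even if improvement is the more likely one.

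The statistical rule adds to the problem. A one-tailed test for improvement has two results: improvement shown, or improvement not shown. If anxiety, depression or burden rose in the intervention arm, or resilience fell, the rule would give no formal way to say so. At stake are the accuracy of what families are told about risk and the trial's ability to draw a conclusion in the direction that the assurance rules out.

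**Working it through.** **1. The assurance against the rest of the article.** Setting and recruitment says no adverse effect, without condition. The Introduction says the programme is untested in this population and still to be validated. The Discussion says effects in this field are uncertain. These cannot all stand; only the first can be changed by rewording.

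**2. The plan's own sample size.** Inputs from Sample size:
- δ = 0.29, a before-after figure ("changed by 0.29 points before and after the intervention")
- power 0.9 ("with a statistical power of 0.9")
- one-tailed α = 0.025
- n = 36 per group, with 10% dropout
- SD: not stated

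The printed formula is n = (Zα + Zβ)² · 2σ² / δ², with Zα + Zβ = 1.960 + 1.282 = 3.242.

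Without σ, the 36 cannot be reproduced independently. Solving backwards: σ = 0.29 × √(36/2) / 3.242 = 0.380, so δ/σ = 0.764. Any σ from about 0.374 to 0.380 rounds up to 36. The dropout step reproduces: 36 / 0.9 = 40.

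**3. Cost of a two-sided test.** One-sided 0.025 and two-sided 0.05 share the critical value 1.960, so n is the same whatever the SD:

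| Assumed SD | n per group, one-sided 0.025 | n per group, two-sided 0.05 |
|---|---|---|
| 0.3 | 23 | 23 |
| 0.375 | 36 | 36 |
| 0.4 | 40 | 40 |
| 0.5 | 63 | 63 |

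**4. What each rule can say about worsening.** Assume a simple comparison of two means in SD units. The standard error is √(2/n): 0.236 for 36 per arm and 0.224 for 40. The probability that a two-sided 95% interval lies wholly on the side of worsening, for a true worsening h, is Φ(h/SE − 1.960).

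| True worsening (SD) | 36 per arm | 40 per arm | One-tailed test for benefit |
|---|---|---|---|
| 0.764 | Φ(3.24 − 1.96) = 0.90 | 0.93 | cannot declare it |
| 0.5 | Φ(2.12 − 1.96) = 0.56 | 0.61 | cannot declare it |
| 0.3 | Φ(1.27 − 1.96) = 0.25 | 0.27 | cannot declare it |

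**5. One-tailed rule against ANOVA.** A t test can be one-tailed. The F test of a repeated measures ANOVA rejects for differences in either direction, so it cannot follow a directional rule. If 0.025 were simply carried over to it, a two-group comparison would amount to a two-sided test at 0.025. That needs 42 per group at SD 0.375 (43 at 0.379), not 36. The section therefore contains two rules that must be reconciled.

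**The case against.** The strongest reply is that the trial does look at the outcomes that matter. Anxiety, depression and burden are measured four times in both arms, with cut-offs, and Statistical analysis promises means, SDs and percentages. Arm means would show the direction of any change. This stands. A reader might infer that nothing in the plan looks for worsening, and the article does not support that.

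Other tempting readings also go too far:
- **That every test is one-tailed for benefit.** The sentence on one-tailed testing names no direction; the direction comes from the Hypotheses. The ANOVA F test is not directional at all.
- **That harm would be reported as no effect.** No reporting rule says so. The Conclusion's contrast between an effective and an ineffective programme is discussion of implications and does not set a decision rule.
- **That the assurance is given before consent.** The timing is not fixed. The sentence follows the description of signing and assignment, and the consent form is not available here.
- **That participants are uneasy with this format.** The Introduction says "people are not used to expressing their feelings and sharing family problems publicly", but this is an argument against multifamily groups and for the one-on-one meetings used here.
- **That adverse-event procedures are missing.** A condensed article may leave these to the full protocol, so the point does not rest on them.

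The article also has protections: opting out at any time, exclusion of people with a history of mental illness, and specialist supervision of delivery. They lower the risk but do not make an unconditional promise true. Nor do descriptive means replace an interval when the question is whether a group got worse.

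**Conclusion.** The point holds in a limited form. The assurance is too absolute, and the article's own account of what is known contradicts it. The one-tailed rule, read with improvement-only hypotheses, leaves no formal way to conclude worsening on any outcome and does not fit the ANOVA named beside it. The data to show worsening will be collected; only the inference is missing.

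The size is illustrative. With 36 completers per arm, two-sided intervals would reveal a worsening of 0.76 SD about 90% of the time, 0.5 SD about 56% and 0.3 SD about 25%. A one-tailed test for benefit would never do so. These figures assume a simple two-mean comparison rather than the ANOVA. The 0.76 is back-solved from n = 36 because no SD is given, and it comes from a resilience calculation, so carrying it over to SAS, SDS or FBSD is a further assumption. The conclusion itself does not depend on the 0.76. Even two-sided intervals would often miss a modest worsening, so an unqualified assurance would not be justified by a clean result either.

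**What to change.** 1. **Setting and recruitment.** Replace the assurance with a neutral statement: the effects of the programme are not yet known, and talking about illness and family problems may be upsetting. Keep the right to opt out at any time.
2. **Sample size and Statistical analysis.** Replace one-tailed 0.025 with two-sided 0.05 in both places. State that the ANOVA is tested at 0.05. Report between-group differences with two-sided 95% intervals for family resilience and every secondary outcome.
3. **Optional.** Tabulate, by arm and visit, how many participants moved up a SAS or SDS severity band since baseline, or newly reached 1 or more on an FBSD dimension.

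The cost is small: no extra families (36 per group, 40 with dropout, are unchanged), no new data, slightly less reassuring wording and, if the option is taken, one extra table.

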### Participants

#### Inclusion criteria for patients

Women with first pathological diagnosis of breast cancer18 years old and olderUndergoing surgeryUsing a smartphoneGood understanding and communication skills, no history of mental illnessInformed consent, willing to cooperate

#### Exclusion criteria for patients

Having other serious medical conditionsParticipation in other psychological interventions

#### Inclusion criteria for family members

A fixed patient caregiver (first-degree relatives)18 years old and olderGood understanding and communication skills, no history of mental illnessUsing a smartphoneInformed consent, willing to cooperate

#### Exclusion criteria for family members

Having serious medical conditionsParticipation in other psychological interventions

### Sample size

Study sample size calculated by PASS15. Based on previous survey results (Lim and Han, 2013), family resilience measured by the Family Resilience Index (FHI) changed by 0.29 points before and after the intervention with a statistical power of 0.9, 2.5% significance, and using a one-tailed test to calculate a sample size of 36 families in each group (72 families in total; McCubbin et al., 1996). Assuming a 10% dropout rate in the intervention, each group would need to include 40 families (80 families in total). The sample size calculation formula is as follows:

$$n=\frac{{\left({Ζ}_{\alpha }+{Ζ}_{\beta }\right)}^{2*}2\sigma^{2}}{\delta^{2}}$$

A series of measures will be taken to reduce attrition during the intervention. First, during the intervention recruitment phase, the patient’s attending physician or other medical staff will be invited to answer the patient’s and family’s concerns to increase participants’ trust in the program. Second, a WeChat group will be established where researchers answer questions and share disease-related knowledge with participants. The third is to invite breast cancer treatment experts and nursing experts to control the quality of the entire intervention process, and timely answer questions from patients and their families about disease treatment and care. Fourth, during the intervention, participants can get in touch with the research team to get answers to any difficulties involved in the implementation and application of the intervention content. Finally, at the end of the program, the research team will present the participants with a nice gift to express their gratitude.

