### Hypotheses

The research hypotheses are as follows:

After the intervention, the family resilience level of the intervention group will be significantly improved compared with that before the intervention.After the intervention, the family resilience level of the intervention group will be significantly improved compared with that of the control group.After the intervention, other aspects related to family resilience in the intervention group, such as the family disease burden and anxiety and depression levels of patients and their families, will be significantly relieved, and the level of disease coping and social support will be improved accordingly.

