#### Outcome: Family resilience

The Chinese version of the Family Resilience Assessment (C-FRA) will be used to assess the family resilience level of the research subjects (Zhang et al., 2021). This scale was developed for family resilience of breast cancer patients and translated into Chinese. It has good reliability and validity in breast cancer patients. The scale contains 5 dimensions and 28 items measured on a 5-point Likert scale. The higher the score is, the better the level of family resilience. Cronbach’s alpha for this scale is 0.961.

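### The stated 90% power rests on a before-after change on the FHI entered into a two-group formula, so it is not shown to apply to the between-group comparison on the C-FRA

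*Protocol article*

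**What the plan says.** **Planning effect.** The Sample size section takes its effect from an earlier study in which family resilience, on an instrument it calls the FHI, "changed by 0.29 points before and after the intervention with a statistical power of 0.9".

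**Error rates and size.** Power is 0.9. The calculation uses "2.5% significance, and using a one-tailed test to calculate a sample size of 36 families in each group". A 10% dropout allowance takes this to 40 per group, 80 families in all. The Statistical analysis section agrees on the level: "SPSS23.0 will be used for data analysis with a one-tailed test and a significance level of 0.025".

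**Formula.** The printed expression is n = (Zα + Zβ)² × 2σ² / δ². No value of σ is printed.

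**Primary outcome.** Under Outcome: Family resilience, "The Chinese version of the Family Resilience Assessment (C-FRA) will be used to assess the family resilience level of the research subjects". It has 28 items on a 5-point scale. Table 2 lists family resilience as the primary outcome.

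**Comparison.** The second hypothesis is that "the family resilience level of the intervention group will be significantly improved compared with that of the control group". The Statistical analysis section assigns the between-group question to repeated measures ANOVA.

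**The concern.** The factor 2σ² identifies the formula as the one for two independent means, and it returns a number per group. In that formula δ has to be the difference between intervention and control on the outcome being analysed. The plan's δ differs from this in two ways:

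- **Kind of effect.** 0.29 is a change within one group over time. It equals a between-group difference only if the control group does not change, or if 0.29 already excludes whatever both groups would gain. The article states neither. Control families receive handbooks, a WeChat group with answers from researchers, and encouragement to support one another. Both groups are also recovering from surgery over the same weeks.
- **Instrument.** 0.29 is in FHI points. The article gives no conversion to C-FRA points and no argument that the standardised effect carries over.

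The 90% is the article's only justification for the trial's size. If the trial finds no difference, readers will take the result as coming from a study with 90% power for its primary comparison, which has not been shown.

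**Working it through.** **Inputs from the protocol article:** one-sided α = 0.025 (Sample size; Statistical analysis), power 0.90, δ = 0.29 FHI points, 36 per group, 10% dropout, 1:1 allocation. σ is not printed, so I solved for it.

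**1. Reproducing the plan's figure.** Zα + Zβ = 1.960 + 1.2816 = 3.2415.

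- Standardised effect implied by n = 36: d = 3.2415 × √(2/36) = 0.764.
- Implied σ = 0.29 / 0.764 = 0.380. At n = 35 it is 0.374, so any σ between these rounds up to 36.
- With the t distribution (70 degrees of freedom), d = 0.775 and σ = 0.29 / 0.775 = 0.374.
- Dropout: 36 / (1 − 0.10) = 40. This step reproduces.

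The plan's 36 is therefore consistent with its formula if σ was about 0.37 to 0.38. Stating σ would complete the arithmetic. It would not change the fact that δ is a before-after change on another scale.

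**2. Could the calculation be for the before-after hypothesis?** A paired formula, n = (Zα + Zβ)² × σ_change² / δ², gives 36 only for an SD of change of 0.53 to 0.54 (√36 × 0.29 / 3.2415 = 0.537; √35 × 0.29 / 3.2415 = 0.529). The printed formula carries the factor 2 and the result is stated per group, so it is a two-group calculation.

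**3. What 36 evaluable families per group provide.** Unadjusted comparison of two means, one-sided 2.5%, with the true between-group C-FRA difference in SD units:

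| Difference (SD) | Power, z | Power, t |
|---|---|---|
| 0.50 | 56% | 55% |
| 0.57 | 68% | 66% |
| 0.77 | 90% | 90% |
| 0.80 | 92% | 92% |

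**4. Illustration: control-group gain.** Two assumptions are made that are not in the article: the intervention group's total gain is 0.29 (d = 0.764), and baseline is not used. If controls gain a fraction f of 0.29, the difference is 0.764 × (1 − f). The last column adds adjustment for baseline C-FRA at an assumed correlation of 0.5, which divides the residual SD by 1/√0.75, that is, multiplies it by √(1 − 0.25) = 0.866.

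| Control gain | Difference (SD) | Power, t, unadjusted | Power, t, baseline-adjusted |
|---|---|---|---|
| none | 0.76 | 89% | 96% |
| one quarter | 0.57 | 67% | 79% |
| one third | 0.51 | 57% | 69% |
| one half | 0.38 | 36% | 45% |

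(The one-quarter row uses 0.573 SD, hence 67% here and 66% at exactly 0.57 in step 3.)

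**5. Detectable difference with baseline adjustment.** At the same assumed correlation, the 90% detectable difference is 0.775 × 0.866 = 0.67 SD.

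**The case against.** The strongest reply accepts the mismatch and disputes what follows from it.

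- **Direction.** The control-gain scenarios all lower power, but the instrument mismatch has no computable direction. The C-FRA was developed for families of breast cancer patients and may respond more or less than the FHI. At 0.80 SD, power is 92%. This stands.
- **Shared gains.** Usual care and recovery reach both groups. If the earlier 0.29 mostly reflects the programme, shared gains cancel and the between-group difference stays near 0.29. Which case applies depends on a study that is not at hand. This stands, and makes the scenarios illustrations only.
- **Planned analysis.** The article plans repeated measures ANOVA over four time points including baseline, not a single unadjusted comparison. Using baseline recovers part of the power, as the last column of step 4 shows, although repeated measures ANOVA is not the same as baseline adjustment. This stands.
- **Which hypothesis.** The Sample size section names none, and a before-after change suits the first hypothesis. This carries little weight, because the printed formula and the per-group result are for two groups.
- **Missing σ.** A condensed article may leave it to the full protocol. Agreed; the point does not rest on it.
- **Few trials to draw on.** Borrowing from a related scale is understandable in a field where the article counts three randomised studies. That explains the choice, but does not make the 90% a property of this comparison.

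A reader might infer that the trial is underpowered, or that its power is really 36% to 67%. The article does not support that: it gives neither an expected C-FRA difference nor an expected control-group change.

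**Conclusion.** The point holds in a limited form. The 90% power is derived from the wrong kind of effect for the formula used, and on a scale other than the primary outcome's. It is therefore not shown to apply to the between-group C-FRA comparison. Actual power is unknown and may lie on either side of 90%.

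The conclusion that needs no outside figure is that 36 evaluable families per group give 90% power, one-sided 2.5%, for a difference of about 0.77 SD (0.764 by the normal formula, 0.775 by the t distribution), unadjusted. The control-gain figures depend on the two assumptions in step 4, and the baseline-adjusted ones also on a correlation of 0.5.

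Severity: should be fixed. It affects how the trial's size is justified and how a null result is read. It does not demonstrate an error in the number of families.

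**What to change.** Keep 80 families. In the Sample size section, drop the FHI before-after change as δ and replace the power statement with wording such as:

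> *36 evaluable families per group give about 90% power (one-sided 2.5%) for a between-group C-FRA difference of 0.77 SD, about 66% for 0.57 SD and 55% for 0.50 SD, in an unadjusted comparison of means.*

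Express the difference in C-FRA points as well once a C-FRA SD can be cited. If the between-group analysis will adjust for baseline C-FRA, add that the 90% detectable difference falls to about 0.67 SD at an assumed correlation of 0.5. If control-gain scenarios are shown, label them illustrative and state their assumptions.

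Cost: one paragraph. Recruitment, allocation and outcomes are unchanged. The drawback is that the stated power reads less favourably, because 90% is then tied to a difference of about three quarters of an SD.
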